### Statistical analysis

Analysis sets are defined as the following:
The intention-to-treat (ITT) population will comprise all randomized infantsThe Per Protocol population will comprise all randomized infants that receive at least one administration of their assigned treatment and who are not deemed ineligible on blinded clinical reviewA second Per Protocol population will comprise all randomized infants who received the minimum required administrations of 14 days of their assigned treatment and who are not deemed ineligible on blinded clinical review.The safety population will comprise all randomized infants who received at least one dose of the assigned treatment. Infants will be analysed according to the treatment they received for the purposes of the safety analysis.

An interim analysis of the primary composite endpoint and of survival to discharge using the Haybittle-Peto [28] approach in the first 250 infants enrolled in the study in Canada. The procedure involves evaluating the test statistic calculated under the null hypothesis against a boundary of 3 standard deviations (equivalent to χ^2^ = 9, with a *p*-value of 0.0027. This will have a negligible effect on the alpha level applicable at the final analysis.

A two sided alpha (significance level) of 5% will be applied to the analysis of the primary composite endpoint. There will be no adjustment for the interim analysis evaluated using the Haybittle-Peto boundary [30].

The key secondary endpoints for LIFT_Canada comprise the individual components of the primary composite (survival, brain injury, NEC, LOS, and ROP). *P*-values adjusted for the 5 comparisons performed for this set of endpoints will be derived using the Benjami-Hochberg procedure [31] with a family wise error rate of 5%. Results of other endpoints, subgroup, and sensitivity analyses will be interpreted in proper context and with due consideration of type 1 error.

The primary analysis in LIFT_Canada is a pooled analysis utilizing the individual data of infants recruited in Canada combined with the data of the infants recruited in the LIFT_ANZ trial. Safety analyses will be performed using the safety population. Non-safety analyses will be performed using the ITT population. Sensitivity analyses will be performed using the Per Protocol populations. In addition, information will be presented as Canadian data only and combined poled (Canada and ANZ) data.

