The primary analysis will be a comparison between treatment groups on the proportion of infants experiencing the primary composite endpoint that is tested using a Wald test (using a χ^2^ distribution) from a log-binomial model fitted using generalized estimating equations to accommodate correlation of data between siblings from multiple births. If the log-binomial model does not converge, a logistic model will be used.

Secondary categorical endpoints will be analysed using the same modelling approach applied to the primary endpoint (i.e. a log-binomial model fitted using the generalized estimating equations to accommodate possible correlation of data between sibling from multiple births; if the log-binomial model does not converge, a logistic model will be used).

A descriptive analysis of adverse events related to the study treatment and those reported to Health Canada in the Canadian cohort will be conducted by treatment allocation. The event rate is expected to be low and an exact test would be the appropriate choice to perform any formal comparisons between the two groups in the proportion experiencing an event related to the study treatment.

Consistency of the treatment effect on the primary endpoint across subgroups will be tested by including a treatment-by-subgroup interaction term (along with the relevant main effect terms) as covariates in the analysis model.

The subgroups of interest are
Birthweight < 1000 g versus 1000-1499 g≤ 28 weeks versus > 28 weeks gestation at birthRandomized ≤72 h versus > 72 h from birthThose who received probiotics by 36 weeks CG (note: this is a post-baseline covariate)Those who received human milk (mother’s own milk or donor human milk) versus formula as initial enteral feeds (note: this is a baseline covariate)

Both human milk as initial feeds and ‘probiotic use by 36 weeks CG are co-variates; an unbiased evaluation of their role as an effect-modifier will be attempted.

Randomisation is stratified by gender, birth weight (< 1000 g vs ≥ 1000-1499 g), single versus multiple birth, and centre. Sensitivity of results obtained from the primary analysis of the primary endpoint to adjustment for stratification factors will be explored by including them as covariates in the model.

Finally, an overall treatment adherence adjusted estimate of the effect of bLF on (i) the primary composite endpoint, and (ii) survival to hospital discharge will be calculated.

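### The 5% family-wise error rate stated for the five key secondary endpoints is not guaranteed by Benjamini-Hochberg, which controls the false discovery rate

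*Protocol article*

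**What the plan says.** All of this is in the Statistical analysis section of the protocol article.

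- **The family.** "The key secondary endpoints for LIFT_Canada comprise the individual components of the primary composite (survival, brain injury, NEC, LOS, and ROP").
- **The adjustment.** P-values are "adjusted for the 5 comparisons performed for this set of endpoints", and are to be "derived using the Benjami-Hochberg procedure [31] with a family wise error rate of 5" per cent.
- **The tests.** "Secondary categorical endpoints will be analysed using the same modelling approach applied to the primary endpoint", that is, a log-binomial model fitted by generalized estimating equations.
- **The primary endpoint.** It is tested separately: "A two sided alpha (significance level) of 5% will be applied to the analysis of the primary composite endpoint".
- **Everything else.** "Results of other endpoints, subgroup, and sensitivity analyses will be interpreted in proper context and with due consideration of type 1 error", so there is no formal adjustment outside the family of five.

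The article does not mention a false discovery rate. It names no second procedure, such as Holm, Hochberg or gatekeeping, that would supply family-wise control.

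**The concern.** The sentence joins a procedure to an error rate that the procedure does not guarantee. The family-wise error rate is the probability of rejecting at least one true null hypothesis. The false discovery rate is the expected share of rejections that are false. Benjamini-Hochberg bounds the second. Each genuine rejection relaxes the threshold applied to the remaining components, so a real effect on one component makes a false claim on another more likely.

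That situation is plausible here. The Background cites review evidence of effects on both sepsis and NEC, and the Discussion singles out late-onset sepsis. The Aim section makes a benefit on each component an explicit objective. If sepsis or NEC is truly affected, a further claim on survival, brain injury or ROP could be reported as protected at a family-wise 5% when it is not.

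**Working it through.** **Inputs.** From the Statistical analysis section: m = 5 tests and a 5% level. Two-sided testing is stated for the primary and assumed here for the components. The number k of truly affected components, their power and the correlation between tests are assumptions.

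**Thresholds at each step**

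| Rank of p (smallest first) | Benjamini-Hochberg, 0.05·i/5 | Holm and Hochberg, 0.05/(5−i+1) |
|---|---|---|
| 1 | 0.010 | 0.0100 |
| 2 | 0.020 | 0.0125 |
| 3 | 0.030 | 0.0167 |
| 4 | 0.040 | 0.0250 |
| 5 | 0.050 | 0.0500 |

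**The stated 5%.** It is reproduced when k = 0: the family-wise error is 0.050 for independent tests. It also holds when k = 4, because the single remaining true null is tested at no more than 0.05. It is not reproduced between these, as follows.

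**Independent tests, affected components certain to be rejected**

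- k = 3, two true nulls. Neither is rejected if the smaller p exceeds 0.04 and the larger exceeds 0.05. That probability is 0.96² − 0.01² = 0.9215, so the family-wise error is 1 − 0.9215 = 0.0785.
- k = 2, three true nulls. None is rejected if the ordered p-values exceed 0.03, 0.04 and 0.05. That probability is 0.95³ + 3(0.02)(0.95²) + 3(0.02² − 0.01²)(0.95) = 0.857375 + 0.054150 + 0.000855 = 0.91238, so the family-wise error is 0.0876.
- k = 1, by simulation: 0.078.

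**Effects of realistic size**

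The article claims more than 80% power for the composite and states none for the components, so two cases were simulated.

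1. About 80% power per affected component (z-shift 2.8, assumed).
2. The effect implied by the LIFT_ANZ sepsis result in the section on the rationale for continuing (relative risk 0.82, 95% CI 0.63-1.07, 1542 infants). The standard error of the log relative risk is (ln 1.07 − ln 0.63)/3.92 = 0.135. Scaled to 1542 + 500 = 2042 infants it is 0.135 × √(1542/2042) = 0.117. If 0.82 is the true value, the expected z is 0.198/0.117 = 1.7.

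Family-wise error of Benjamini-Hochberg (at least 500,000 runs per case):

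| Components affected | Near-certain rejection, correlation 0 / 0.3 | About 80% power, correlation 0 / 0.3 | z = 1.7, correlation 0 / 0.3 |
|---|---|---|---|
| 1 | 0.078 / 0.075 | 0.066 / 0.062 | 0.050 / 0.050 |
| 2 | 0.088 / 0.084 | 0.072 / 0.067 | 0.046 / 0.047 |
| 3 | 0.079 / 0.077 | 0.064 / 0.060 | 0.037 / 0.039 |
| 4 | 0.050 / 0.050 | 0.041 / 0.039 | 0.022 / 0.024 |

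With no component affected the values are 0.050 and 0.048. In the runs at no effect, 80% power and near-certain rejection, Holm and Hochberg stayed at or below 0.050 within simulation error, and the false discovery rate of Benjamini-Hochberg lay between 0.010 and 0.050. For scale, five unadjusted independent tests at 0.05 give 1 − 0.95⁵ = 0.226.

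**A set of p-values that separates the methods:** 0.013, 0.02, 0.03, 0.04, 0.20.

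- Benjamini-Hochberg: the fourth value, 0.04, meets its threshold of 0.04, so the first four are rejected.
- Holm: the smallest, 0.013, exceeds 0.01, so none is rejected.
- Hochberg: 0.20 > 0.05, 0.04 > 0.025, 0.03 > 0.0167, 0.02 > 0.0125 and 0.013 > 0.01, so none is rejected.

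**The case against.** The strongest reply is that this is a slip of terminology with little practical effect. The named procedure is well defined and can be run as written. Controlling the false discovery rate is a legitimate choice for the components of a composite. On the article's own sepsis figures the family-wise error does not exceed about 5%. The figures near 8-9% need components that are almost sure to be rejected, and even the 6-7% band assumes power per component that the article does not claim.

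Much of this stands. It bears on size and severity, and it makes relabelling as good a remedy as a change of method. It does not make the sentence right: a family-wise rate is a guarantee over all configurations of true and false nulls, and this procedure does not give it.

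Three stronger readings are tempting and are not supported.

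- A reader might infer that the family-wise error exceeds 5% whenever bLF affects any component. It does not with four affected, nor at z of about 1.7.
- A reader might infer that the trial's main conclusion is at risk. The primary composite has its own two-sided 5% test, which this sentence does not touch.
- A reader might take the misspelt name beside a family-wise rate as proof that Hochberg's step-up was intended. The article does not settle whether the procedure or the error rate is the slip.

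**Conclusion.** The point holds as a misstatement of moderate severity. The method and the error rate attached to it do not match, and nothing else in the article corrects this. The excess over 5% is about 1 to 2 percentage points when one to three components are affected at about 80% power, and at most about 4 points (8.8% against 5%) when rejection of the affected components is nearly certain. There is essentially no excess with no component affected, with four affected, or with effects as weak as the LIFT_ANZ sepsis estimate.

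These sizes rest on assumed power, on independent tests or a common correlation of 0.3, and on two-sided component tests. That Benjamini-Hochberg does not guarantee a 5% family-wise error rests on none of them. The analysis plan, which is not to hand, may name the error rate correctly, but the published sentence is wrong as it stands.

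**What to change.** Before unblinding, change the one sentence in either of two ways, and carry the same wording into the analysis plan.

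- **Keep the procedure.** State that Benjamini-Hochberg is applied to the five components at a false discovery rate of 5%, and make no family-wise claim for them in the report. Thresholds and analysis do not change. The cost is a weaker statement about any single component.
- **Keep the error rate.** State that Holm-adjusted p-values are used for the five components at a family-wise 5%, or Hochberg-adjusted p-values if its dependence condition is accepted. The cost is stricter thresholds at the middle ranks: 0.0125, 0.0167 and 0.025 in place of 0.02, 0.03 and 0.04.

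The choice should follow from which guarantee the sponsor wants for component claims. Correct the spelling of the procedure's name at the same time, so that Benjamini-Hochberg and Hochberg cannot be confused. Neither option affects the sample size, the primary test or the conduct of the trial.

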### Collaboration with LIFT_Australia/New Zealand (LIFT_ANZ)

The Canadian-funded component of LIFT (LIFT_Canada) will enroll 500 participants to add to the 1542 participants already enrolled in LIFT_ANZ. By combining over 2000 recruited infants, the combined LIFT will have > 80% power to detect a 19% reduction in death or serious morbidity from a control rate of 26 to 19.5% at 2-tailed *p* < 0.05, which is clinically important, plausible, and more conservative than earlier trial results.

If LIFT confirms a 19% reduction in the RR of its primary outcome, bLF will have a major impact, translating into thousands more intact survivors without major morbidity in Australia, New Zealand, Canada, Europe and worldwide each year. As> 90% of very preterm survivors at hospital discharge reach adulthood [19, 20], this represents more than 19,000 life-years gained in Canada alone each year, one of the largest gains in intact survival - in any specialty - since neonatal surfactant and antenatal steroids [21, 22]. In addition, by following the infants to 24 months corrected age (CA), information on neurodevelopmental outcomes which is currently lacking will also be provided as survival without major morbidity has been associated with an improved chance of a positive neurodevelopmental outcome by 2 years corrected age [23].

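### The logistic fallback for a non-converging log-binomial GEE changes the effect measure from relative risk to odds ratio; this matters mainly for the stratification-adjusted sensitivity analysis

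*Protocol article*

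**What the plan says.** Under Statistical analysis, the protocol article bases the primary comparison on a Wald test from a "log-binomial model fitted using generalized estimating equations to accommodate correlation of data between siblings from multiple births". The next sentence gives the fallback: "If the log-binomial model does not converge, a logistic model will be used". The rule is then extended: "Secondary categorical endpoints will be analysed using the same modelling approach applied to the primary endpoint", with the logistic fallback repeated in brackets. The same section plans interaction tests for five two-level subgroups, and a sensitivity analysis that adds the stratification factors (gender, birth weight, single or multiple birth, centre) to the model.

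The section on collaboration with LIFT_ANZ frames the design on the RR scale: "If LIFT confirms a 19% reduction in the RR of its primary outcome". It gives the rates as "from a control rate of 26 to 19.5" per cent. The earlier trials and meta-analyses in the Background are also summarised mainly as risk ratios. The article states no step that would return a logistic result to an RR. Nor does it say that an OR would be reported or read as an RR.

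**The concern.** The log link gives an RR and the logit link gives an OR. Under the stated rule, which of them is estimated depends on whether an algorithm converges and not on the question asked. With about a quarter of control infants expected to have the event, an OR lies clearly further from 1 than the RR for the same two risks. An OR set against the RR target, the earlier trials' RRs, or another analysis of this trial on the RR scale would differ from them even if the data agreed perfectly.

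This matters most for a sensitivity analysis, whose only purpose is comparison with the primary result. If the primary estimate is an RR and the adjusted estimate is an OR, the difference between them mixes the effect of adjustment with the change of scale.

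**Working it through.** **Inputs.** Control rate 26%, treated rate 19.5%, stated reduction 19%, and N = 500 + 1542 = 2042, all from the section on collaboration with LIFT_ANZ. Allocation is 1:1 (Randomisation), so n = 1021 per arm. Alpha is 0.05 two-sided (Statistical analysis).

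**The plan's own figure.** The article claims "> 80% power to detect a 19% reduction in death or serious morbidity". Power = Φ{[|p1 − p2|√n − 1.96√(2p̄(1 − p̄))] / √[p1(1 − p1) + p2(1 − p2)]}.
- 26% to 19.5%: RR = 0.195/0.26 = 0.75, a 25% reduction; power 93.9%.
- A true 19% reduction: p2 = 0.26 × 0.81 = 0.2106; power 74.9%.

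The sentence does not reproduce as a whole, so the RR the trial is designed on is ambiguous. That is a separate matter. Both readings are carried below.

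**RR to OR.** OR = [p2/(1 − p2)] / [0.26/0.74], where 0.26/0.74 = 0.3514.

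| Treated risk | RR | OR | Reduction in risk | Reduction in odds | log OR / log RR |
|---|---|---|---|---|---|
| 21.06% | 0.81 | 0.2668/0.3514 = 0.759 | 19% | 24.1% | 1.31 |
| 19.5% | 0.75 | 0.2422/0.3514 = 0.689 | 25% | 31.1% | 1.29 |

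Conversely, OR 0.81 gives treated odds 0.3514 × 0.81 = 0.2846, hence a risk of 0.2215 and RR 0.852.

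**Does the test change?** With n = 1021 per arm and siblings ignored, SE(log RR) = √[(1 − p2)/(n p2) + 0.74/(0.26n)] and SE(log OR) = √[1/(n p2(1 − p2)) + 1/(n × 0.26 × 0.74)].
- RR 0.81: z = -2.62 (log RR) against -2.63 (log OR).
- RR 0.75: z = -3.48 against -3.49.

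**Which models could trigger the fallback?** The usual cause of log-binomial failure is a fitted risk pushed above 1.
- *Treatment only (primary and secondary).* There are two fitted risks, one per arm. In 200 simulated trials with risks of 26% and 21.06%, and about 25% of infants assumed to come from twin pairs, the GEE converged every time. The geometric mean estimates were RR 0.809 and OR 0.758. The log-binomial and logistic tests disagreed on significance in 0.5% of trials.
- *Treatment by binary subgroup.* Both main effects plus the interaction give four cells and four parameters, so fitted risks are essentially the observed proportions. With assumed stratum risks of 44% and 14% in a 40/60 mix (0.4 × 44% + 0.6 × 14% = 26%), 100 of 100 simulated fits converged.
- *Adjusted for gender, birth weight, multiplicity and centre.* This model is not saturated, and additive log-risks for many centres can push a fitted risk above 1. Two simulations assumed 10 to 30 centres and no sibling clustering. Failure rates were 0% to 23% in one. In the other, with between-centre SD 0.3 to 0.5 on the logit scale, they were about 3% to 36%. The adjusted OR was near 0.74 in the first and 0.72 to 0.73 in the second; the adjusted RR was near 0.82 and 0.80 to 0.81.

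The unadjusted 0.81 would therefore sit beside an adjusted OR of about 0.74. The step from 0.81 to 0.76 is scale alone. The remainder arises because ORs are non-collapsible: conditioning on prognostic covariates moves them even without confounding. The adjusted RR stayed close to 0.81, so adjustment itself changed little.

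**The case against.** The strongest case on the other side has five parts.

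1. *The primary result is safe.* This stands. The treatment-only model should converge, and if it did not, RR = 1 and OR = 1 are the same null hypothesis and the test statistic is nearly identical.
2. *The subgroup models are safe.* This also stands. A reader might infer that the fallback would create spurious interactions: a constant RR of 0.81 at the assumed risks of 44% and 14% gives ORs of 0.705 and 0.786. The arithmetic is right, but the interaction models as specified are saturated and are very unlikely to reach the fallback. For the same reason a table mixing RRs and ORs across the secondary endpoints is unlikely.
3. *An OR is not an overstatement.* This stands in part. An OR of 0.76 is valid in itself and exaggerates only when read as, or against, an RR. The article does not say that it would be. But the adjusted analysis exists to be set beside the primary one, so that comparison is built in.
4. *This is detail for the analysis plan.* Convergence criteria, working correlation and conversion to an RR could well be left there, and a plan not shown may add a conversion. But the article does not leave the fallback open. It names it twice, and the one it names changes the effect measure.
5. *A pre-specified logistic fallback is an objective rule.* True, and it prevents a choice after seeing the data. A fallback that keeps the RR would be just as objective.

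**Conclusion.** The point holds in limited form. The stated fallback changes the effect measure in a trial framed on the RR. At a 26% control rate the apparent reduction would grow by about 5 to 6 percentage points (19% to 24.1%, or 25% to 31.1%), whichever of the two design figures is meant. The documents do not support the wider inference that the primary finding, its p-value or the subgroup tests are at risk.

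The realistic exposure is the sensitivity analysis with centre and the other stratification factors, where an adjusted OR of about 0.74 beside an unadjusted RR of about 0.81 could be mistaken for sensitivity to adjustment. This rests on two assumptions: that the fallback carries over to that analysis, which the article implies by describing it as the primary model with added covariates, and that centre numbers and between-centre variation resemble those simulated, since the article gives neither. The failure rates are therefore indicative only. The RR-to-OR conversion needs only the article's own rates. This is a cheap improvement to the plan, not a threat to its main conclusion.

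**What to change.** Replace the logistic fallback with a modified Poisson GEE: log link, robust variance, the same sibling clusters. State that it applies to the primary, secondary, subgroup and adjusted models alike, so that every analysis reports an RR. If the logistic model is kept, state that a marginal RR standardised from it will be reported. Settle this before unblinding, so that the reported measure cannot depend on convergence.

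The cost is one sentence and standard software, with no change to trial conduct. There are two small downsides. Fitted risks may exceed 1 in the Poisson model, which matters little when only the treatment RR is wanted. Standardisation needs a little extra work for its standard error, which must respect the sibling clusters.

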### Rationale for continuing LIFT_Canada

Earlier in 2019, two large trials presented results, the Enteral Lactoferrin supplementation for very preterm infants (ELFIN trial) [24, 25] and Lactoferrin for Infant Feeding Trial_Australia New Zealand (LIFT_ANZ) [26].

In 2203 infants in the ELFIN Trial (2203 infants), lactoferrin was associated with a relative risk (risk ratio) for late onset sepsis of 0.95 (95% CI 0.86–1.04) [25]. This confidence interval did not reliably exclude a 14% reduction or a 4% increase in sepsis. In the 1417 infants in ELFIN who received formula for > 50% of days of enteral feeds, lactoferrin was associated with a relative risk for sepsis of 0.89 (95% CI 0.79–1.01). This did not reliably exclude a 21% reduction or 1% increase in sepsis in this subgroup. Overall, ELFIN did not rule out important potential benefits, particularly for infants who receive formula for over half of days of enteral feeds.

In 1542 infants in LIFT_ANZ, lactoferrin was associated with a relative risk for late onset sepsis of 0.82 (95% CI 0.63–1.07). LIFT_ ANZ did not rule out a 37% reduction or 7% increase in sepsis. (Presented at the 7th International Conference on Clinical Neonatology, Torino, Italy, May 2019).

When ELFIN is combined with LIFT_ANZ and all other trials, a total of 5011 infants, the overall effect of lactoferrin is to reduce the relative risk of late onset sepsis to 0.82 (95% 0.74–0.92; *P* = 0.0004), with moderate heterogeneity (I^2^ = 0.58) and asymmetric funnel plot, consistent with small study effects (personal communication, [name]).

Similarly, a meta-analysis of the effect of bLF on late onset sepsis in 1891 preterm infants who were not fed exclusively mother’s own milk in two RCTs of bLF supplementation [25, 27, 28], a relative risk of late onset sepsis to be reduced to 0.82 (95% 0.71–0.96; *P* = 0.01), with moderate heterogeneity (I^2^ = 0.64) and asymmetric funnel plot, consistent with small study effects, or true differences between trials in effectiveness or underlying patient risk [29].

This is consistent with a more moderate but clinically relevant average benefit in reducing sepsis with no evidence of harm and no clear increase in mortality, NEC, sepsis or other adverse outcomes. Consequently, a decision to continue enrollment has been supported by the Steering Committee for LIFT_Canada and LIFT_ANZ.

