### Design

LIFT_Canada is a multi-centre, double-masked, randomized controlled trial with an intention-to-treat analysis. The aim is to enroll 500 infants whose data will be combined with the data of the 1542 infants enrolled from LIFT_ANZ in a pooled analysis (see Fig. 1 for study flow). Eligible infants will be randomized and allocated to one of two treatment groups: 1) a daily dose of 200 mg/kg bLF in breast/donor human milk or formula milk until 34 weeks CG or for a minimum of 2 weeks, whichever is longer, or until discharge home or transfer, if earlier; 2) no bLF with daily feeds.

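### The primary analysis pools two trials, but no treatment-by-trial term is planned, so the trials are not formally compared and a between-trial difference could be credited to a subgroup

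*Protocol article*

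**What the plan says.** The Design section sets out to "enroll 500 infants whose data will be combined with the data of the 1542 infants enrolled from LIFT_ANZ in a pooled analysis". The Statistical analysis section makes that pool primary: "The primary analysis in LIFT_Canada is a pooled analysis utilizing the individual data of infants recruited in Canada combined with the data". The primary model is a log-binomial model fitted by generalized estimating equations to allow for siblings, with a logistic fallback. No trial term is named.

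On effect modification, the same section says: "Consistency of the treatment effect on the primary endpoint across subgroups will be tested by including a treatment-by-subgroup interaction term". Only the relevant main effects accompany that term. The five subgroups are birth weight, gestation, age at randomisation, probiotic use by 36 weeks and type of initial feed. Neither trial nor country is listed. Centre appears only among the stratification factors, which enter as covariates in a sensitivity analysis of the primary endpoint. That analysis does not let the treatment effect vary by trial.

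On display, the section says: "information will be presented as Canadian data only and combined poled (Canada and ANZ) data".

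**The concern.** Two things are at stake.

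- **The main claim.** When two separately run trials are pooled for one primary result, readers will ask whether the trials agree, all the more because LIFT_ANZ had presented its results while Canada was still enrolling. The plan shows material from which agreement can be judged, but it specifies no estimate or test of the difference.
- **The subgroup claims.** The article plans to attempt an unbiased evaluation of human milk and probiotics as effect modifiers, and its Discussion suggests that benefit may be greater alongside them. Probiotic use, initial feed and age at randomisation depend on local practice and may differ between countries. In the pool, a model with only treatment, subgroup and their interaction mixes within-trial and between-trial information. If the effect differs by trial for another reason, part of that difference goes to whichever subgroup is more common in one trial.

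**Working it through.** **Inputs from the article.** 1542 and 500 infants, taken as 771 and 250 per arm (1021 per arm pooled); control rate 26%; two-sided 5% level. **Assumptions.** Trial-specific risk ratios (RRs) and subgroup prevalences, for which the article gives no figures. Sibling clustering is ignored.

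**The plan's own figure.** The article says "the combined LIFT will have > 80% power to detect" its target effect, worded as "detect a 19% reduction in death or serious morbidity from a control rate of 26 to 19.5" percent. Those rates are a 25% relative reduction (1 - 19.5/26), for which 1021 per arm gives 93.9% power. A true 19% reduction (26% to 21.06%) gives 74.9%. The mismatch is a separate matter, and nothing below depends on it beyond the 26% control rate.

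**Step 1: how the false subgroup effect arises.** Take a subgroup with prevalence 30% in ANZ and 90% in Canada, RR 1.0 in ANZ and 0.6 in Canada, and no subgroup effect within either trial.

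- Subgroup present, per arm: 771 × 0.3 = 231.3 (ANZ) and 250 × 0.9 = 225 (Canada). Pooled RR = (231.3 × 1.0 + 225 × 0.6)/456.3 = 0.80.
- Subgroup absent: 539.7 and 25. Pooled RR = (539.7 × 1.0 + 25 × 0.6)/564.7 = 0.98.
- Apparent ratio of RRs = 0.80/0.98 = 0.82, where the true within-trial ratio is 1.

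**Step 2: how often the 5% test rejects.** Each row rests on 2000 simulated pooled datasets, with a log-link model, robust variance and no true within-trial interaction.

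| Prevalence ANZ/Canada | RR ANZ/Canada | Stated model rejects | With trial and treatment-by-trial | False ratio of RRs, stated model |
|---|---|---|---|---|
| all four pairs below | 0.81/0.81 | 4.5-5.1% | 4.4-5.2% | about 1.00 |
| 50/50% | 1.0/0.6 | 5.5% | 5.6% | 1.00 |
| 50/80% | 0.95/0.75 | 6.1% | 4.9% | 0.95 |
| 50/80% | 1.0/0.6 | 9.2% | 4.9% | 0.91 |
| 30/90% | 0.95/0.75 | 11.2% | 5.4% | 0.90 |
| 30/90% | 1.0/0.6 | 23.8% | 5.1% | 0.82 |
| 10/90% | 0.95/0.75 | 16.4% | 5.6% | 0.84 |
| 10/90% | 1.0/0.6 | 44.9% | 4.7% | 0.71 |

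A further mild case (50/90%, RR 0.95/0.75; 1000 datasets) gave 7.5% and a false ratio of 0.93. Monte Carlo standard errors are about 1 percentage point or less.

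**Step 3: illustration for the main claim.** Assume ANZ RR 0.92 and Canada RR 0.60. The variance of log RR per trial is (1-pc)/(n·pc) + (1-pt)/(n·pt).

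- ANZ: pt = 0.2392; 0.74/200.46 + 0.7608/184.42 = 0.00782; SE 0.088; 95% CI 0.77-1.09.
- Canada: pt = 0.156; 0.74/65 + 0.844/39 = 0.03303; SE 0.182.
- Inverse-variance pool: weights 127.9 and 30.3; log RR = (127.9 × (-0.0834) + 30.3 × (-0.5108))/158.2 = -0.165; SE = 1/√158.2 = 0.0795; RR 0.85 (0.73-0.99).
- Trial difference: SE = √(0.00782 + 0.03303) = 0.202; z = 0.427/0.202 = 2.1; ratio of RRs 0.60/0.92 = 0.65 (0.44-0.97).

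The pooled result is nominally positive, the ANZ interval spans 1, and the planned analyses do not formally test the difference.

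**Step 4: power of a trial test.** The SE of the log ratio is 0.187 when both RRs are 0.81, and 0.201 at 1.0/0.6. Power is 24% for 0.95/0.75, 52% for 0.9/0.6 and 72% for 1.0/0.6. For 80% power the ratio must be about exp(-2.80 × 0.187) = 0.59.

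**The case against.** **Condensed article.** The article does not say that trial is excluded from the models, and the full analysis plan may add the terms. This stands as a limit. Even so, the article fixes both the form of the consistency model and the subgroup list, and neither contains the factor that defines the pool.

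**Two unproven conditions.** The false subgroup effect needs the trial effects and the subgroup mix to differ together. The article quantifies neither, the error stays near 5% if either is absent, and mild cases are small. This stands.

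**Existing caution.** The article already promises that subgroup results will be read with type 1 error in mind, and it flags probiotic use as post-baseline. That tempers the interpretation but does not separate within-trial from between-trial information.

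Three stronger readings are tempting, and the article supports none of them.

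- A reader might infer that the sponsor itself suspects that the LIFT trials differ, from "or true differences between trials in effectiveness or underlying patient risk". That sentence concerns late-onset sepsis in a meta-analysis of two trials cited as [25, 27, 28]. LIFT_ANZ is cited as [26], and the outcome is one component of the composite. It is general background only.
- A reader might infer that disagreement would be hidden. The pool is Canada plus ANZ, so the ANZ counts follow by subtraction, and LIFT_ANZ has presented results of its own. What is missing is a planned comparison.
- A reader might infer that the pooled primary test is invalid. Against the hypothesis of no effect in either trial it remains valid.

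**Conclusion.** The point holds as a limited, conditional one. The stated consistency test and subgroup models contain no treatment-by-trial term, so the two trials are not formally compared and subgroup interactions are not confined to within-trial information. Where effects and subgroup mix both differ by trial, the assumed scenarios put the rejection rate of the nominal 5% test at about 6-7.5% (mild), 9-16% (intermediate) and 24-45% (extreme). Adding the terms returns it to about 5%. The extreme figures need RRs of 1.0 and 0.6 with prevalence gaps of 60 to 80 percentage points, and nothing in the article says that such gaps exist. The main-claim example is an illustration, not a forecast. The change is a worthwhile, inexpensive improvement to interpretation. It corrects no error in the primary comparison.

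**What to change.** In the Statistical analysis section, or in the analysis plan if that is where the models are finally fixed:

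1. Add trial (LIFT_ANZ or LIFT_Canada) as a consistency factor. Report the ANZ, Canadian and pooled RRs side by side, with the ratio of RRs and its confidence interval. State that this test has low power (SE of the log ratio about 0.18-0.20), is read through its interval, and does not gate the primary result.
2. Include trial and treatment-by-trial terms in every subgroup model, so that each subgroup interaction is estimated within trials.

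**Cost.** Some wording and a few model lines; the primary estimate is unchanged. Subgroup interaction intervals widen by roughly 1/√(1-r²), where r is the correlation between subgroup and trial. With 24.5% of infants in Canada (500/2042) and prevalences of 40/90%, the overall prevalence is 0.755 × 0.4 + 0.245 × 0.9 = 0.522. Then r² = 0.755 × 0.245 × 0.5² / (0.522 × 0.478) = 0.185, a widening of about 11%; simulation gave about 10% (SE 0.159 to 0.175). The same formula gives about 4% at 50/80% and about 50% at 10/90%. In that last case the data hold little within-trial information on the subgroup, and the wider interval says so. The added terms do not cure the separate difficulty that probiotic use is measured after randomisation.
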